**Fig. 1 Fig1:**
[figure not shown]
Design of the study

**Fig. 2 Fig2:**
[figure not shown]
SPIRIT figure

### Statistical analysis and sample size

Time to reach FEF, the primary outcome, will be analyzed by Kaplan and Meier survival analysis according to the intention-to-treat principle. The two arms will be compared with the log-rank Test [36].

Regarding secondary outcomes, the time to reach half enteral feeding and time to reach full oral feeding will be estimated by Kaplan and Meier analysis, the failure of the respiratory support assigned at randomization will be compared using Fischer’s exact test, and the other secondary outcomes will be estimated using appropriate generalized linear models. This will be a single-blind trial where the blinded person will be the statistician.

Based on a population of infants with a gestational age < 30 weeks who are consecutively admitted to the NICUs of each research unit from January to June 2017 (mean time of FEF 19.6 days) and considering a ratio between the subjects of the two arms of 1:1, a sample size of at least 141 patients per arm has been calculated to observe a difference of 30% between the two arms (5.7 days).

An interim analysis is planned upon reaching the enrollment of half of the patients expected by the sample size calculation.

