## Abstract

**Background:**

Respiratory distress syndrome (RDS) and feeding intolerance are common conditions in preterm infants and among the major causes of neonatal mortality and morbidity.

For many years, preterm infants with RDS have been treated with mechanical ventilation, increasing risks of acute lung injury and bronchopulmonary dysplasia.

In recent years non-invasive ventilation techniques have been developed. Showing similar efficacy and risk of bronchopulmonary dysplasia, nasal continuous positive airway pressure (NCPAP) and heated humidified high-flow nasal cannula (HHHFNC) have become the most widespread techniques in neonatal intensive care units. However, their impact on nutrition, particularly on feeding tolerance and risk of complications, is still unknown in preterm infants.

The aim of the study is to evaluate the impact of NCPAP vs HHHFNC on enteral feeding and to identify the most suitable technique for preterm infants with RDS.

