## Background

Respiratory distress syndrome (RDS) is a common condition in premature infants and one of the major causes of neonatal mortality [1]. For many years, preterm infants with RDS have been treated with mechanical ventilation, increasing the risks of acute lung injury and long-term morbidity, such as bronchopulmonary dysplasia (BPD) [2–5]. Offering an appropriate respiratory support in the delivery room, together with early surfactant administration, can allow one to avoid or limit endotracheal ventilation with better outcomes in terms of mortality and short- and long-term complications, above all BPD [6]. Early nasal continuous positive airway pressure (NCPAP) treatment combined with surfactant replacement therapy decreases the need for mechanical ventilation and has been recommended as the first line treatment for RDS [7, 8]. However, NCPAP has significant limitations, mainly related to the type of interface needed. Excessive leaks around the prongs or mask and through the mouth can lead to inadequate support, whereas excessive pressure may result in pneumothorax and damage to the nose and face. Moreover, the bulky fixation devices obscure the infant’s face, interfering with both feeding and positioning [9]. In recent years, heated humidified high-flow nasal cannula (HHHFNC) has been studied as an alternative non-invasive respiratory support (NRS). HHHFNC became popular partially due to some perceived advantages related to the type of interface used. Cannulas are easier to apply than NCPAP prongs or mask, may be more comfortable for infants, and may enable easier access to babies’ faces, thus facilitating feeding and parental bonding [10–12]. Whereas the practical advantages seem to be established, there is controversy about HHHFNC efficacy as respiratory support [13–15]. Recent studies support that HHHFNC is as effective as NCPAP for the primary treatment of RDS, but evidences are still insufficient and data are still lacking, especially for the extremely preterm population (< 28 weeks’ gestation) [14, 16–18]. A recent Cochrane review comparing HHHFNC with other NRS measures showed equivalent rates of treatment failure and similar rates of BPD when used as a post-extubation support in preterm infants [19]. With equivalent effectiveness, the choice of the most adequate NRS should consider the impact on the health status of the premature infant, evaluating above all the effect on nutrition and growth. Along with RDS, feeding intolerance (FI) represents a relevant issue in preterm infants, and the coexistence of the two represents a great challenge for the neonatologist [20]. Because of gastrointestinal immaturity, a considerable proportion of premature infants will develop clinical symptoms of FI, causing interruptions of feeding. This delays the establishment of adequate enteral nutrition and prolongs the need for parenteral nutrition, thus increasing the risk of infections and prolonging hospital stay [21]. Avoiding FI and its complications, such as necrotizing enterocolitis (NEC), is a priority for the neonatologist, who often faces the challenge of interpreting the clinical and prognostic significance of common and aspecific signs of FI. Clear identification of the parameters that should be evaluated to identify FI is still lacking in the literature, although, among controversy, the presence of gastric residuals, vomits and/or regurgitations, and abdominal distension and the onset of crises of apnea/bradycardia are considered the most frequent signs [22, 23]. A correlation between non-invasive ventilation and the occurrence of FI and NEC is plausible, although the mechanisms through which ventilation may induce FI and its incidence in ventilated infants are still unclear [20, 24]. The most common hypothesis is that pressurized gases that are not completely conveyed to the airways could cause bowel distension. Bowel distension in infants on CPAP was described by Jaile et al. [25] as *CPAP belly syndrome*, but no inferences about feeding tolerance and risk of NEC were drawn. More recent studies evaluated the effect of CPAP on mesenteric flow and gastric emptying, suggesting a role of CPAP as a risk factor for FI [26–28]. No specific studies have been designed to evaluate the impact of different types of NRS on FI and the occurrence of NEC, which are generally evaluated as secondary outcomes, susceptible to data analysis and patient selection biases. Our hypothesis is that different techniques of NRS may have different impacts on feeding issues in preterm infants.

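### Failure of the assigned respiratory support is tied to an unstratified Fisher test of no difference, which cannot show how large an excess of failure the trial excludes, although the case for choosing on feeding rests on equivalent effectiveness

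*Protocol article*

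**What the plan says.** Four parts of the protocol article bear on this point.

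- **Aim.** The Abstract wants to compare the two techniques on enteral feeding and "to identify the most suitable technique for preterm infants with RDS". The Aims section adds a further aim: to evaluate the response to both techniques as RDS treatment in extremely preterm infants.
- **Rationale.** The Background states: "With equivalent effectiveness, the choice of the most adequate NRS should consider the impact on the health status of the premature infant". It reports recent studies and a systematic review in favour of similar effectiveness. The review concerns post-extubation use. For primary treatment it says that "evidences are still insufficient and data are still lacking, especially for the extremely preterm population", meaning below 28 weeks.
- **Randomisation.** Recruitment and randomization describes block randomisation that balances infants below 28 weeks and those at 28 weeks or more between the arms within each unit.
- **Analysis.** Statistical analysis and sample size states that "the failure of the respiratory support assigned at randomization will be compared using" Fisher's exact test. It names no stratification, effect measure or interval for this outcome. The size of 141 per arm is set for time to full enteral feeding (FEF). Secondary outcomes other than failure and the two feeding times go to generalized linear models that are not described further.

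**The concern.** If a technique is to be preferred because infants feed sooner on it, the reader needs to know that it does not fail materially more often as respiratory support. That is a question about the size of a possible excess. Fisher's test answers another question, whether the data are compatible with no difference at all. A non-significant result may mean that the arms are alike, or that the trial was too small to tell.

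The protocol itself says that effectiveness is least certain below 28 weeks, and infants of 25-27 weeks are a large part of the eligible range. A faster-feeding technique could therefore be reported beside a non-significant failure comparison while the data still allow a substantial excess of failure. The reader could not tell from the p-value.

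**Working it through.** **Inputs from the protocol.** n = 141 per arm and 1:1 allocation (Statistical analysis and sample size); failure recorded as yes/no (Table 4).

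**Inputs not given, so assumed.** Two-sided alpha of 5%; failure of 5% to 25% in the better arm; a 10-point excess as an illustration. Enrolment requires at least 48 h of stability (Inclusion criteria), so rates below 10% are plausible and are kept in the range.

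**1. The plan's own figure.** The protocol states no power, rate or margin for failure, so there is none to reproduce. The 141 concerns time to FEF, and alpha, power and SD are not stated for it either. As a rough check, a hazard ratio of 0.70 at two-sided 5% and 85% power needs 4(1.960 + 1.036)²/(ln 0.70)² = 283 events, close to 282 infants if every infant has the event. Failure does not enter that calculation.

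**2. Power of Fisher's test for a 10-point excess.** Let x and y be the failures in each arm. Power is the sum of Bin(x; 141, p) × Bin(y; 141, p + 0.10) over all pairs (x, y) whose two-sided Fisher p-value is at most 0.05. The 95% half-width for the risk difference at equal rates is 1.96 × √(2p(1 − p)/141); at p = 0.10 this is 1.96 × √(0.18/141) = 0.070.

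| Failure, better v worse arm | Power | Missed | 95% half-width if both arms fail at the lower rate |
|---|---|---|---|
| 5% v 15% | 0.765 | 23.5% | 5.1 points |
| 10% v 20% | 0.598 | 40.2% | 7.0 points |
| 15% v 25% | 0.502 | 49.8% | 8.3 points |
| 20% v 30% | 0.442 | 55.8% | 9.3 points |
| 25% v 35% | 0.399 | 60.1% | 10.1 points |

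**3. What a non-significant result can conceal.** Suppose 28/141 (19.9%) fail in one arm. The largest count in the other arm that stays non-significant is 43/141 (30.5%), with Fisher p = 0.054.

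- Difference: 15/141 = 10.6 points.
- Standard error: √(0.199 × 0.801/141 + 0.305 × 0.695/141) = 0.0513.
- 95% Wald interval: 10.6 ± 1.96 × 5.13, or 0.6 to 20.7 points.

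The p-value alone reads as no significant difference, while the interval runs up to about 21 points. Its lower limit lies just above zero because Fisher's test is more conservative than the Wald interval.

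**4. Below 28 weeks.** The protocol does not give the share of these infants. If it were half, about 70 per arm, the same calculation gives power of 41% at a 5% rate, 30% at 10% and 20% at 25% for a 10-point excess. The half-width 1.96 × √(2p(1 − p)/70) is 7.2, 9.9 and 14.4 points at those rates.

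**The case against.** The strongest case on the other side has five parts.

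- **No stated misreading.** A reader might infer that the investigators will take p > 0.05 as proof of equivalence. The protocol does not say this. The Background draws the premise from published evidence, and the Discussion says only that the trial could clarify efficacy. This stands. The point is limited to what the named test can deliver.
- **Not the only evidence on effectiveness.** A reader might infer that Fisher's test is the sole respiratory analysis. Table 4 also lists duration of assigned support, total duration of support, bronchopulmonary dysplasia and pneumothorax, and generalized linear models can give estimates with intervals for these. This stands too. Fisher's test is the only specific test named for failure of the assigned support.
- **Detail left to a fuller plan.** Naming a test does not rule out an interval, and an article need not list every summary. That is fair about the silence on an interval, which alone would be no finding. But the article does fix the method for this outcome, a test of difference without the randomisation strata, and that choice can be judged as it stands.
- **Low power on a secondary outcome is ordinary.** True, and the 40-60% depends on assumed rates. The finding is not that the trial should be sized for failure. Limited power is the reason to report an interval rather than a p-value.
- **A binding margin would change the design.** With an illustrative 10-point margin, one-sided 2.5% and truly equal arms, power at 141 per arm would be about 97% at a 5% rate, 80% at 10%, 65% at 15%, 55% at 20% and 49% at 25%. A margin that gates the conclusion would often block it when nothing is wrong, and statisticians would differ on imposing one. This stands, so no such gate is asked for.

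**Conclusion.** The concern holds in a limited form. The argument for choosing on feeding depends on respiratory effectiveness being equivalent, and the protocol calls that evidence insufficient, especially below 28 weeks. The analysis it fixes for failure of the assigned support cannot say how large an excess the data exclude, and it ignores the gestational-age groups used at randomisation.

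The size depends on inputs that the protocol does not supply. The 40-60% miss rate is not a property of the trial as such: it applies to a 10-point excess, a two-sided 5% level and failure of 10-25% in the better arm. At 5% failure the miss rate is about 24%.

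The documents do not support the stronger readings that the protocol plans to declare equivalence from non-significance, or that a formal non-inferiority margin is required. The analysis of time to FEF is unaffected. This is a worthwhile improvement to a safety-relevant secondary analysis.

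**What to change.** In Statistical analysis and sample size:

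1. Analyse failure of the assigned support as a risk difference, HHHFNC minus NCPAP, with a 95% confidence interval, stratified by the gestational-age groups used at randomisation (below 28 weeks; 28 weeks or more). Mantel-Haenszel weights would serve.
2. Report the same difference and interval for infants below 28 weeks, where the Aims section asks about respiratory response.
3. Keep Fisher's test as a supplementary p-value, and name the interval as the main result, since the two can disagree near the 5% level.
4. State that a non-significant difference will not be read as equivalent effectiveness, and that any statement about the most suitable technique will be made alongside this interval.

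Whether to add a margin that must be met before a technique is recommended is for the investigators to decide.

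The cost is a few sentences, with no new data or patients. The downside is that at this size the interval may be too wide to support equivalence, particularly below 28 weeks, and the report would have to say so.

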### Inclusion criteria

All infants admitted to the NICUs with a gestational age between 25 and 29 weeks and who will have met the following inclusion criteria will be consecutively enrolled in the study:Presence of RDSPeriod of stability on HHHFNC or NCPAP for at least 48 h in the first 5 days of life (SatO_2 TC_ 90–95%, pCO_2_ ≤ 60 mmHg, FiO_2_ < 40%, Silverman score [29] ≤ 6, ≤ 2 apnea episodes/h with CPAP ≤7 cmH_2_O if on NCPAP, and flow ≤7 L/min if on HHHFNC)≤ 7 days of lifeSuitability to start enteral feeding (if already started it should be less than 75 mL/Kg/day)Parental written consent

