### Outcomes

The primary outcome of the study is the time needed to reach FEF, defined as an enteral intake of 150 mL/Kg/day. Secondary outcomes are listed in Table 4.

**Table 4 Tab4:** Secondary outcomes

– Time to reach HEF, defined as an enteral intake of 75 mL/Kg/day (days) – Interruptions of enteral feeding (episodes/day) – Not given feeds (episodes/day) – Pathologic gastric residual volumes (episodes/day) – Vomits and/or regurgitations (episodes/day) – Abdominal distention (mean score/day) – Beginning of oral feeding (post-menstrual age) – Time to reach full oral feeding (number of days) – Post-menstrual age at full oral feeding (weeks) – Weight growth (∆ z-score) – Duration of the respiratory support assigned at randomization (days) – Total duration of respiratory support need (days) – Failure of the respiratory support assigned at randomization (yes/no) – Length of hospital stay (days) – Duration of central venous catheter (days) – Clinical events and complications (NEC, bowel perforation, pneumothorax, BPD, PDA, ROP, IVH, PVL) – Transfers to other hospitals or deaths before reaching full enteral feeding (number of patients)	

*HEF* half enteral feeding, *NEC* necrotizing enterocolitis, *BPD* bronchopulmonary dysplasia, *PDA* patent ductus arteriosus, *ROP* retinopathy of prematurity, *IVH* intraventricular hemorrhage, *PVL* periventricular leukomalacia

The design of the study is outlined in Fig. 1. The Standard Protocol Items: Recommendations for Interventional Trials (SPIRIT) figure of enrollment, interventions, and assessments is shown in Fig. 2. The SPIRIT checklist is provided as Additional file 1.

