## Discussion

The identification of the most suitable NRS technique for preterm infants with RDS and FI could reduce gastrointestinal complications, improve growth, and reduce hospital stay, thus improving quality of life of infants and their family and reducing health costs.

The evaluation of the timing of oral feeding could be useful in understanding the influence that NRS techniques have on the development of sucking-swallowing coordination.

A standard protocol for the suspension of feeding will be proposed along with a new clinical score to evaluate signs of FI. It may be useful to evaluate the influence, on clinical practice and on the time of achievement of FEF, of the application of a defined and shared method for the evaluation of feeding tolerance. The authors considered a difference of 30% in the time to reach FEF between the groups as the minimum needed to observe a clinically relevant effect. As a consequence, the sample of this study was set at 141 patients per arm.

The evaluation of the response to NCPAP and HHHFNC could clarify their efficacy as treatment for RDS in extremely preterm infants.

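### The target difference does not match its own inputs: 30% of the 19.6-day mean is 5.9 days, not 5.7 days (wrong as written, minor)

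*Protocol article*

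**What the plan says.** The Statistical analysis and sample size section of the protocol article takes its planning value from earlier admissions to the participating units ("mean time of FEF 19.6 days"). With equal allocation, "a sample size of at least 141 patients per arm has been calculated" in order "to observe a difference of 30% between the two arms (5.7 days"). The mean, the percentage and the day figure all stand in the same sentence.

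The Discussion returns to the percentage but gives no days: "The authors considered a difference of 30% in the time to reach FEF between the groups as the minimum needed" for clinical relevance. It then presents 141 per arm as the consequence of that choice.

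**The concern.** The day figure is offered as the equivalent of the percentage, and it is not. The sentence is the article's only quantitative basis for 141 per arm, and the 30% also serves as its threshold of clinical relevance. If the size of the trial rests on 30%, the printed day figure is a slip. If it rests on 5.7 days, the trial was sized for an effect slightly smaller than the stated threshold. If the mean was really 19.0 days, the planning value is misprinted. A reader checking the calculation, or later judging an observed difference in days against the target, needs to know which of these holds.

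**Working it through.** **Inputs from the article.** Mean 19.6 days; difference 30%, given as 5.7 days; 141 per arm, so 2 × 141 = 282 infants.

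**1. Trying to reproduce 5.7 days.**
- Direct: 0.30 × 19.6 = 5.88 days. The gap is 5.88 − 5.70 = 0.18 day, and 0.18 / 5.88 = 3.1%.
- In reverse: 5.7 / 19.6 = 29.1%, and 5.7 / 0.30 = 19.0 days.
- Rounding of the mean: 19.55 to 19.65 days gives 5.87 to 5.90 days.
- Rounding of both inputs downwards: 0.295 × 19.55 = 5.77, which rounds to 5.8.
- 19.6 read as the slower arm's mean under a 1.3 ratio: 19.6 − 19.6/1.3 = 4.52.
- 19.6 read as the faster arm's mean under a 0.7 ratio: 19.6/0.7 − 19.6 = 8.40.
- 19.6 read as the average of both arms: 6.92 (ratio 0.7) or 5.11 (ratio 1.3).

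None of these gives 5.7.

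**2. Does 141 show which figure was used?** Alpha, power, spread and allowance for loss are not in the article, so what follows is assumed: two-sided 5% and exponential times, so that the hazard ratio equals the ratio of means. Schoenfeld's formula for 1:1 allocation is events = 4(z₁ + z₂)² / (ln HR)², where z₁ = 1.96 and z₂ is the normal quantile for the power.
- 30%: ln 0.70 = −0.3567. At 85% power, 4(1.960 + 1.036)² / 0.1272 = 282.3 events, or 141.2 per arm with no loss.
- 30%, Freedman's formula, 80% power, 10% loss: 253 events, and 253 / (2 × 0.9) = 140.6 per arm.
- 29.1%: HR = 13.9 / 19.6 = 0.709. Schoenfeld at 80% power with 5% loss: 266 events, and 266 / (2 × 0.95) = 140.0 per arm.

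Several sets of assumptions land on or next to 141, under either effect. The number alone does not settle the matter.

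**3. What the slip is worth.** Under the same model, power = Φ(½√events × |ln HR| − 1.96).
- 282 events, 30%: ½ × 16.79 × 0.3567 − 1.96 = 1.03, so power is 85.0%.
- 282 events, 29.1%: ½ × 16.79 × 0.3436 − 1.96 = 0.93, so power is 82.3%.
- Events for 80% power: 247 against 266, a ratio of 1.08.

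If the planning was instead on a difference in means with a fixed standard deviation, the number per arm varies with 1/difference²:
- 141 computed for 5.7 days: 141 × (5.7/5.88)² = 132.5, so 5.88 days needs 133.
- 141 computed for 5.88 days: 141 × (5.88/5.7)² = 150.04, so 5.7 days needs 151.

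**The case against.** **The percentage is the driver and the days are only a gloss.** The section leads with 30%, the Discussion ties 141 to it, and a 30% reduction gives about 141 per arm under one ordinary set of assumptions. This largely stands. It makes 5.9 days the likely correction, and it means the slip is no evidence that the trial is the wrong size. It does not make the printed figure right.

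**The power figures depend on a doubtful model.** The feeding criteria cap progression at 30 mL/kg/day, so going from zero to 150 takes at least 150/30 = 5 days. An exponential with mean 19.6 days would put 1 − exp(−5/19.6), about 22%, at FEF before then. With a less dispersed time (Weibull shape 2, assumed), 80% power needs about 247/4 = 62 events for 30% and 266/4 = 67 for 29.1%. This also stands: the absolute figures are illustrative. The ratio of about 1.08 between the two is the same for any common Weibull shape.

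**A reader might infer more, namely that the target is on the wrong clock.** Infants are randomised some days after birth, whereas the 2017 cohort was never randomised. But the article gives no time origin for the 19.6 days or for the primary outcome ("The primary outcome of the study is the time needed to reach FEF"). A mismatch therefore cannot be shown, and a condensed article may leave the origin to the full protocol.

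**A reader might also infer that the planning cohort contradicts the trial population.** The cohort was "infants with a gestational age < 30 weeks who are consecutively admitted to the NICUs of each research unit from January to June 2017", with no respiratory, stability or exclusion filter stated. The eligibility text begins "All infants admitted to the NICUs with a gestational age between 25 and 29 weeks" and adds several such conditions. The cohort is broader, but it is openly described, and the upper limits agree if 29 means completed weeks. The size and direction of any bias cannot be computed from the article. This is at most a limitation.

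**Conclusion.** Wrong as written, minor. That the mean, the percentage and the day figure conflict is certain and needs no assumption. The gap is 0.18 day, or 0.9 percentage points of effect (30% against 29.1%).

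Its effect on the design is modest: under 3 points of power in the exponential log-rank illustration, or 133 to 151 per arm around 141 if the planning was on means. Both rest on the assumed alpha and model, and the log-rank figure also assumes that every infant reaches FEF. Neither shows that 141 is too small. That 5.9 days is the intended figure is an inference from the Discussion; only the authors' calculation record can confirm it.

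**What to change.** Check the record of the sample-size calculation and correct whichever figure was not used:
- If 30% of 19.6 days was used, print 5.9 days.
- If 5.7 days was used, print 29% and align the statement of clinical relevance in the Discussion.
- If the mean was 19.0 days, correct the mean.

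In each case, confirm that 141 per arm follows from the corrected input. The cost is one sentence (two if the percentage changes) and a look at a calculation already done. It calls for no change in the number of infants and no new data.
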